#### *Additional safety measures*

A single non-blinded CHDR staff member unconnected to the study will receive reports on Hb concentration and Ht of the subjects. This individual will be responsible for the dosage adjustments. If Ht exceeds 52% in a subject, dosage will be stopped and if necessary, ±0.5L blood will be collected from that subject to rearrange a normal Ht percentage. This subject will then be excluded from the study.

(Serious) Adverse Events ((S)AEs) will be collected throughout the study.

### **6.3 Exploratory endpoints**

- RNA expression levels in venous blood before and after a submaximal exercise test

## 7 STUDY ASSESSMENTS

See Table 1 for the time points of the assessments.

### 7.1 Exercise-specific screening assessments

#### 7.1.1 Exercise test

For the exercise test at screening, a ramp protocol will be followed until exhaustion. The details of the test will be described in the exercise manual.

#### 7.1.2 Questionnaire

Please refer to appendix 4.

### 7.2 Safety and tolerability assessments

The definitions, reporting and follow-up of AEs and SAEs are described in section 8.

#### 7.2.1 Specific safety assessments

A single non-blinded CHDR staff member unconnected to the study will receive reports on the haemoglobin (Hb) concentration and haematocrit (Ht) of the subjects. This individual will be responsible for the dosage adjustments.

If Ht exceeds 52% in a subject, dosage will be stopped and if necessary,  $\pm 0.5$ L blood will be collected from that subject to correct the Ht percentage to a normal level. This subject will then be excluded from the study.

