**16. Safety endpoints**

Safety will be assessed by:

1. Physical examination
2. Monitoring vital signs
  - Pulse Rate (bpm)
  - Systolic blood pressure (mmHg)
  - Diastolic blood pressure (mmHg)
  - Temperature measurements (°C)
3. Electrocardiogram (ECG)
  - Heart Rate (HR) (bpm), PR, QRS, QT, QTcB
4. Clinical Laboratory Assessments
  - Haematology
 

*Ht must be <52%. If Ht level is ≥52%, therapy should be interrupted until the Ht percentage begins to fall.*

*Hb must be below a certain level (see Figure 1). If Hb exceeds that level, therapy should be interrupted until the Hb concentration falls back into the range.*
  - Chemistry
  - Urinalysis
  - Coagulation
5. Collection of treatment-emergent (serious) adverse events ((S)AEs)

*1-4 will be assessed during screening, 2-5 will be assessed at each clinical visit and before the competition. 2 and 3 will be assessed before and during the exercise tests.*

*(Serious) Adverse Events ((S)AEs) will be collected throughout the study.*

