### **Stopping criteria**

Dosing will be interrupted if

- Ht  $\geq$  52%
- Hb exceeds the upper limit of the target range (see Figure 1)
- there's an unacceptable tolerability profile based on the nature, frequency, and intensity of observed AEs

These criteria will be maintained by the non-blinded CHDR staff member unconnected to the study.

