## **6.2 Safety endpoints**

*Safety measurements before NeoRecormon/placebo administration*

Safety will be assessed by:

- ❖ Monitoring vital signs
  - o Pulse Rate (bpm)
  - o Systolic blood pressure (mmHg)
  - o Diastolic blood pressure (mmHg)
  - o Temperature measurements (°C)
- ❖ Electrocardiogram (ECG) (at rest)
  - o Heart Rate (HR) (bpm), PR, QRS, QT, QTcB
- ❖ Clinical Laboratory Assessments
  - o Haematology
    - Ht must be <52%. If Ht level is ≥52%, therapy should be interrupted until the Ht level begins to fall.*
    - Hb must be below 1.15\*Initial Hb (see Figure 1). If Hb is above that level, dosage should be interrupted until the Hb concentration falls back into the range. Then the dosage should be restarted at 2000IU/week of the previous dose.*
  - o Chemistry
  - o Urinalysis
  - o Coagulation

In addition a single non blinded CHDR staff member unconnected to the study will receive reports on the Hb and Ht of the subjects. This individual will be responsible for the dosage adjustments.

Procedure for dosage adjustment:

When the Hb and/or Ht exceeds a certain value (see 5.3) the dose adjustment officer will issue a request for a dosage change for the subject that requires the change. This request will be for the subject that requires the change in treatment but will also be issued to a random placebo subject to preserve the blinding of the study.

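### The haematocrit rule contradicts itself above 52%, and the exclusion it contains would fall almost only on active-arm subjects with the highest attained haematocrit

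*Protocol*

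**What the plan says.** **Interrupt.** Synopsis section 16: "If Ht level is ≥52%, therapy should be interrupted until the Ht percentage begins to fall". The first part of section 6.2 repeats it: "If Ht level is ≥52%, therapy should be interrupted until the Ht level begins to fall". Section 1.4.6, under Stopping criteria, opens its list with "Dosing will be interrupted if" and puts Ht of 52% or more first. Section 1.4.1 also speaks only of interruption. Neither 1.4.6 nor 1.4.1 mentions exclusion.

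**Stop and exclude.** Section 6.2, Additional safety measures: "If Ht exceeds 52% in a subject, dosage will be stopped". It then provides for about half a litre of blood to be taken if necessary, followed by exclusion. Section 7.2.1 repeats this, with the blood taken "from that subject to correct the Ht percentage to a normal level. This subject will then be excluded from the study".

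**Related wording on haemoglobin (Hb).** For Hb above its own upper limit, section 6.2 says "Then the dosage should be restarted at 2000IU/week of the previous dose". The Dosage Rationale in section 1.4.6 gives a restart at 2000 IU/week with no reference to a previous dose.

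**Data handling.** Section 9.5.2 keeps every randomised and dosed subject who has at least one post-baseline value of the parameter. Section 9.4 does not impute missing results but leaves missing efficacy data to the mixed model. Section 4.6.3 replaces only first-week withdrawals that are not due to adverse events or tolerability.

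**The concern.** The person who adjusts doses has two incompatible instructions for the same subject on a safety threshold that is checked before every weekly dose. One lets the subject continue in the trial after a pause; the other ends his participation.

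The second instruction also has a statistical consequence. A high Ht during the trial is what the active drug is meant to produce. Leaving the study because of it is a post-randomisation event that depends on treatment and would hardly occur on placebo. Visits lost in this way are lost selectively, which can bias the NeoRecormon minus placebo contrast for every endpoint measured later.

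**Working it through.** **1. The two rules side by side.**

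| Ht before dosing | Synopsis 16; 6.2 first part | 1.4.1; 1.4.6 | 6.2 Additional safety measures; 7.2.1 |
|---|---|---|---|
| Below 52% | no Ht action | no Ht action | no Ht action |
| Exactly 52% | interrupt until Ht falls | interrupt | no action |
| Above 52% | interrupt until Ht falls | interrupt | stop, bleed if necessary, exclude |

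The two cannot be read as successive tiers, because they share the same threshold: apart from a reading of exactly 52%, every value that triggers one triggers the other. In the stop rule the sentence on exclusion follows the conditional blood collection, so it can mean everyone above 52% or only those who are bled.

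**2. Is the limit within reach?** Inputs: entry Ht below 48% (section 4.3); expected Hb rise 10-15% (section 1.4.3); limit 52%. Section 1.4.3 makes a ceiling check for Hb, 9.8 × 1.15 = 11.27 mmol/l, which reproduces. It makes no such check for Ht. Assuming Ht rises in proportion to Hb:

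- 52 / 1.15 = 45.2%: a man starting above this reaches 52% within his target range.
- 52 / 1.10 = 47.3%: a man starting above this reaches 52% before the lower end of the range.
- At the entry limit: 48 × 1.10 = 52.8% and 48 × 1.15 = 55.2%.
- Placebo: 52 − 48 = 4, so a rise of more than 4 points is needed without drug.

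**3. Who is selected?** The limit is absolute. A man starting at 47.9% reaches it after a rise of 52 / 47.9 − 1 = 8.6%, which is below the target range. A man starting at 44% with a full 15% rise reaches 44 × 1.15 = 50.6% and stays. Selection is on attained Ht: high baseline, large rise, or both.

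**4. What is lost?** By the schedule in section 3.1, an excluded man misses whichever of these are still to come: ramp tests (last one days 53-56), the time-to-exhaustion (TTE) test (days 46-49) and the race (days 57-60). Section 9.9.1 analyses single measurements with an unpaired t-test and baseline-to-end parameters with a one-way ANCOVA; both drop a man whose value is missing. The mixed model for repeated measurements contains treatment, time, their interaction, baseline and random effects, but no on-treatment Ht. For performance endpoints it corrects the loss only as far as the performance values already observed carry the same information as Ht.

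**5. Illustration of size; every input assumed.** Baseline Ht mean 43, 44.5 or 46 (SD 2, limited to 39-48); rise mean 10, 12.5 or 15% (SD 4 points); Ht measurement SD 0.7; everyone above 52% excluded; VO2max SD 1.95. Expected exclusions were 1.2 to 13.1 of 24 active subjects and practically none on placebo, against 24 − 22 = 2 losses per arm allowed for in section 1.4.9.1. If later values were simply missing, the shift in a complete-case contrast, against the planned 1.5 ml/min/kg, was:

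- correlation 0 between Ht rise and VO2max gain: 0;
- correlation 0.5: −0.07 to −0.57;
- correlation 0.8: −0.11 to −0.91 ml/min/kg.

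Interruptions under the Hb ceiling were not modelled, so both the counts and the shifts lie at the upper end.

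**The case against.** The strongest reply is that this is an editing conflict with little statistical consequence. One unblinded person makes all dose adjustments (section 5.6.2), so staff will not diverge. Figure 1 holds the dosing scheme and is not shown here. The Hb ceiling of 1.15 times the initial value will pause dosing in many men before Ht reaches 52%. If only bled subjects are excluded, there may be very few. Section 9.5.2 keeps all data from before exclusion. Much of this stands, and it limits the statistical consequence. It does not remove the contradiction: a single person still has two instructions, and no figure can make the quoted sentences agree. The Hb ceiling is relative to each man's own start, so it does not protect those with a high baseline Ht.

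A reader might infer that the rule strips the strongest responders from the active arm, and might size the bias by deleting the top few of 24. The documents do not support that. The limit acts on absolute Ht, so baseline matters about as much as response. Earlier data are retained. That the loss falls on the active arm is an inference from the entry limit; the text names no arm. Nor does section 1.4.6 say that dosing resumes after a high Ht: its restart sentence concerns the Hb range, and resumption is implied only in synopsis section 16 and the first part of section 6.2. The restart wording in section 6.2 is likewise an Hb matter and a secondary wording conflict.

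**Conclusion.** The contradiction is established from the text alone and needs no assumption. Every Ht above 52% falls under both rules, and the scope of the exclusion is ambiguous.

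The statistical consequence follows in direction. If exclusion is applied, it will fall almost only on active-arm men with the highest attained Ht, and it will remove their later ramp tests, the week-7 TTE test or the race. This rests on the 48% entry limit and on Ht rising roughly in proportion to Hb. Its size cannot be fixed from the documents: it depends on baseline Ht, on how often the Hb ceiling acts first, on which reading of the exclusion is used, and on how closely Ht response tracks performance. With no such relation the bias is zero. The simulated figures show only that it need not be negligible.

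**What to change.** Reconcile synopsis section 16, sections 1.4.1 and 1.4.6, both parts of section 6.2 and section 7.2.1 into one Ht rule, stated once and cross-referenced elsewhere. It should use one threshold and make clear to whom each step applies. Align the Hb restart wording in section 6.2 with section 1.4.6 at the same time. Which clinical rule is kept is for the sponsor and the investigator; this review does not say.

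Separately from the dosing rule, state that meeting the Ht criterion is not by itself a reason to remove a subject from follow-up or analysis. Assessments already scheduled continue where the investigator considers them appropriate, all data collected are analysed as randomised, and the number of such subjects is reported by arm.

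Cost: a protocol amendment, probably a substantial one under section 10.6.2 because it touches the dose regimen. No subjects are added, and no assessments beyond those already scheduled. The downside is that the estimate will include some data obtained after dosing was interrupted or stopped, which should be said when it is interpreted.

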#### 7.2.2 Vital signs

Evaluations of systolic and diastolic blood pressure, pulse rate and temperature will be performed throughout the study. Pulse and blood pressure will be taken after 5 minutes in the supine position. Automated oscillometric blood pressures will be measured using a Dash 3000, Dash 4000, Dynamap 400 or Dynamap ProCare 400. Additionally, the pulse rate data provided by the pulse oximeter attached to the monitor.

#### 7.2.3 Weight and height

Weight (kg) will be recorded at screening, before each exercise test and the follow-up visit or upon early termination. Height (cm) will be recorded and body mass index (BMI) calculated at screening.

#### 7.2.4 Physical examination

Physical examination (i.e., inspection, percussion, palpation and auscultation) is performed during the course of the study. Clinically relevant findings that are present prior to study drug initiation must be recorded with the subject's Medical History. Clinically relevant findings found after study drug initiation and meeting the definition of an AE (new AE or worsening of previously existing condition) must be recorded.

#### 7.2.5 Electrocardiography

12-lead electrocardiographs (ECGs) will be obtained during the course of the study using Marquette 800/5500 or Dash3000 and stored using the MUSE Cardiology Information System. The investigator will assess the ECG recording as 'normal', 'abnormal - not clinically significant', or 'abnormal - clinically significant' and include a description of the abnormality as required. The ECG parameters assessed will include heart rate, PR, QRS, QT, and QTcB (calculated using Bazett's method).

#### 7.2.6 Laboratory assessments

##### *Laboratory parameters*

Blood and other biological samples will be collected for the following clinical laboratory tests:

| Lab         | Tests                                                                  | Collection & Analysis                                 |
|-------------|------------------------------------------------------------------------|-------------------------------------------------------|
| Haematology | Haemoglobin [including Mean Corpuscular volume (MCV), Mean corpuscular | 4 mL of venous blood in a BD Vacutainer® K2EDTA tube. |

|                            |                                                                                                                                                                                                                                                                                                                                                                                                                                                            |                                                                                                                                                                                                       |
|----------------------------|------------------------------------------------------------------------------------------------------------------------------------------------------------------------------------------------------------------------------------------------------------------------------------------------------------------------------------------------------------------------------------------------------------------------------------------------------------|-------------------------------------------------------------------------------------------------------------------------------------------------------------------------------------------------------|
|                            | haemoglobin (MCH), Mean corpuscular haemoglobin concentration (MCHC), haematocrit, red cell count (RBC), Red cell distribution width (standard deviation) (RDW-SD), reticulocyte count (RET#), reticulocytes percentage (RET%), immature reticulocyte fraction (IRF), total white cell count (WBC), leukocyte differential count and Platelet count. Differential blood count, including: basophils, eosinophils, neutrophils, lymphocytes, and monocytes. | Samples will be analysed by the Central Clinical Hematology Laboratory (CKHL) of Leiden University Medical Center.                                                                                    |
| Chemistry and electrolytes | Sodium, potassium, calcium, inorganic phosphate, total protein, albumin, triglycerides, blood urea nitrogen (BUN), creatinine, ferritin, creatinine phosphokinase (CPK)*, uric acid, total bilirubin  , alkaline phosphatase, AST, ALT, gamma-GT, LDH, C-reactive protein*.                                                                                                                                                                    | 8.5 mL or 2 mL of venous blood in a BD Vacutainer® SST Gel and Clot Activator tube. Samples will be analysed by the Central Clinical Chemistry Laboratory (CKCL) of Leiden University Medical Center. |
| Coagulation                | APTT*, PT*, fibrinogen, D-dimer, F1+2, bTG, PF4, P-selectin, E-selectin, thrombomodulin, TXB2, TNF-alfa                                                                                                                                                                                                                                                                                                                                                    | 2.7 mL of venous blood in a 3.2% citrate BD Vacutainer and 4 mL in CTAD. Samples will be analysed by Good Biomarker Sciences (GBS) in Leiden and labs to be determined.                               |
| RNA expression             | RNA profiles                                                                                                                                                                                                                                                                                                                                                                                                                                               | 2.5 mL of venous blood in PAXgene vacuum tubes using a blood collection system analysed by Leiden Genome Technology Center (LUMC)                                                                     |
| Serology                   | HIV1 and HIV2 antibodies, Hepatitis B antigen and Hepatitis C antibodies                                                                                                                                                                                                                                                                                                                                                                                   | 5 mL of venous blood in a BD Vacutainer® SST Gel and Clot Activator tube. Samples will be analysed by the Central Clinical Microbiology Laboratory (CKML) of the Leiden University Medical Center.    |
| Urinalysis                 | Leucocytes, blood, nitrite, protein, urobilinogen, bilirubin, pH, specific gravity, ketones, glucose. If there is a clinically significant positive result, urine will be sent to the CKCL for microscopy and/or culture.                                                                                                                                                                                                                                  | A midstream, clean-catch urine specimen will be analysed by dipstick (Multistix® 10 SG, Siemens Healthcare Diagnostics, Frimley, UK).                                                                 |
| Alcohol                    | Alcohol Breath Test                                                                                                                                                                                                                                                                                                                                                                                                                                        | The hand-held Alco-Sensor IV meter (Honac, Apeldoorn, the Netherlands) will be used to measure the breath ethanol concentrations.                                                                     |
| Urine drug screen          | Cocaine, amphetamines, opiates (morphine), benzodiazepines, methamphetamine, MDMA and cannabinoids.                                                                                                                                                                                                                                                                                                                                                        | A urine specimen will be analysed at CHDR by test kit (InstAlert, Innovacon, San Diego, USA).                                                                                                         |

Conjugated bilirubin will be reported only when total bilirubin is outside the reference range.

\*Part of the short chemistry/coagulation panel

The results of the haematology assessment will be used for the safety report and for the athlete's biological passport.

### **7.3 Efficacy assessments**

#### **7.3.1 Exercise tests**

Please refer to Appendix 5 – Exercise test for a detailed description of the exercise tests.

#### **7.3.2 Competition**

Please refer to Appendix 6 – Competition for a detailed description of the competition.

#### **7.3.3 Athlete biological passport**

This assessment has already been performed for safety measurements. The results will be used for the safety report and for the athlete's biological passport.

Further calculated markers specific to the Haematological Module of the ABP include OFF-hr Score (OFFS), which is a combination of Hb and RET%, and Abnormal Blood Profile Score (ABPS), which is a combination of Ht, Hb, RBC, RET%, MCV, MCH, and MCHC.

#### **7.3.4 Blood flow**

LSCI measures:

- basal blood flow
- blood flow upon occlusion-reperfusion
- Blood flow after 'exercise'

Forearm blood flow will be measured by non-invasive laser speckle contrast imaging (LSCI; PeriCam PSI System, Perimed). At baseline and after 7 weeks of dosing, the flow will be measured at rest, during a five minute occlusion of the brachial artery and during reperfusion after the occlusion. Blood flow will be measured after exercise at 6 weeks. Procedures for LSCI, brachial artery occlusion-reperfusion are described in SOPs. Briefly, the subject will be seated with the left arm placed on a (table) rest. A suitable area of the volar side of the forearm will be identified. This area will be 'illuminated' by the laser and the response signal will be captured.

